### Toxicity

Pre-defined adverse events will be reported with severity grades according to CTCAE. The radiotherapy applied in this trial could be associated with the following expected acute and sub-acute events: skin toxicity, alopecia, conjunctivitis, otitis, headache, vomiting, nausea, vertigo, fatigue, increase of lesion edema with consequent neurologic symptoms (e.g. aphasia, hemiparesis, cranial nerves disorders, cerebellar disorders, epileptic disorders), disturbances of wound healing after surgery. Systemic therapies (chemotherapy, immunotherapy, targeted therapies) are paused 1 week prior irradiation in order to minimize cumulative toxicity. An independent data safety monitoring committee, consisting of 2 physicians, a physicist and a statistician, is to be provided with all necessary information to review the specified adverse events by means of annual line listings.

### Biological specimens/pharmacogenetic studies (Medical center – University of Freiburg)

During clinical routine blood withdrawing, 20 ml Ethylenediaminetetraacetic acid blood and 8 ml blood in a Blue Tiger Top tube will be collected in the Medical Center – University of Freiburg only, at 4 distinct time points (before start of WBRT, after the last fraction, 6 weeks and 3 months after WBRT) after obtaining separate informed consent. Blood samples will be used to analyze circulating immune biomarkers as predictors of treatment response.

### Statistical planning and analysis

The sample size calculation is based on the primary outcome, which is defined as the difference between the learning scale of the VLMT (word count, 0–75 words) in survivors at 3 months after radiation therapy and at baseline.

Assuming a mean decline after WBRT+SIB of 15 words in VLMT and a common standard deviation of 15 words [6], the study is planned to reject the null-hypothesis of equality of treatment arms with 80% power on the basis of a two-sample t-test at a one-sided significance level of 10% if the deterioration of NCF improves to a 7 words decline after HA-WBRT+SIB. Under these assumptions, 66 patients are required for analysis. According to the patients’ prognosis, we expect about 55% of patients in both arms to survive until 3 months after radiation, plus some additional drop-out of patients unwilling or unable to perform the test. We reckon that 50% of randomized patients will be available for analysis. Therefore, 132 patients should be randomized.

In the primary analysis, differences between HA-WBRT+SIB and WBRT+SIB with respect to the primary endpoint will be estimated and tested within a linear regression model in patients who survive until 3 months after radiation therapy. The model will include treatment and study center as independent variables and will adjust for the baseline learning scale word count of the VLMT. In case of endpoint values missing for reasons other than patient death, these will be handled by multiple imputation. The primary analysis population is the per-protocol set, defined as the group of randomized patients who had no major violations of eligibility criteria and who received treatment as per protocol according to their randomized arm. Sensitivity analyses of the primary endpoint as pre-defined in the study protocol will be performed.

Descriptive and explorative statistical analyses will be performed with respect to the secondary efficacy endpoints. Overall, PFS rates in the two treatment arms will be estimated by the Kaplan-Meier method, and the corresponding endpoints will be analyzed with the Cox model.

For safety analyses, rates of adverse events and the use of corticosteroids will be calculated with 95% confidence intervals.

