## Background

Brain metastases are the most common intracranial tumors in adults, occurring in 10–30% of patients with systemic malignancies [1]. For patients with multiple brain metastases, whole brain radiation therapy (WBRT) remains the primary treatment modality [2].

WBRT was shown to significantly improve distant intracerebral tumor control and reduce the rate of neurological death compared to radiosurgery alone [3], leading to the assumption of relevant microscopic tumor infiltration of the brain. Consequently, the whole brain can be considered a clinical target volume (CTV) and would benefit from a moderate radiation dose [3].

However, WBRT is associated with long-term side effects. Patients receiving additional WBRT after local therapy reported significantly poorer quality of life (QoL) scores than patients receiving local therapy only [4]. The differences were clinically relevant as early as 8 weeks after treatment. The main culprit are neurocognitive deficits frequently observed after WBRT of multiple brain metastases, with episodic memory being the predominant cognitive domain affected [5–7]. Memory deficits are correlated with and precede decreased quality of life [8], and thus play an essential role in patients’ subjective well-being. Although other factors contribute to memory decline, such as age, tumor growth or medication, WBRT has clearly been demonstrated to significantly impair memory [5, 9].

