### Study population

The target population for this trial consists in patients with at least 4 brain metastases of solid tumors, with at least one, but not exceeding 10 metastases ≥5 mm (i.e., eligible for dose escalation). No gender ratio has been stipulated in this study as the results of the preclinical and/or clinical studies did not indicate any difference in the effect of the study treatment in terms of efficacy and safety. However, patients over the age of 80 are excluded, as NCF tests have not been validated for older age cohorts.

Inclusion criteria to be met at the time of registration/randomisation are:
Patient’s written informed consent obtained,Age 18–80 years, male or female,Legal capacity, patient is able to understand the nature, significance, and consequences of the trial,At least 4 brain metastases of solid tumors, with at least one, but not exceeding 10 metastases ≥5 mm (i.e., eligible for dose escalation),Recursive partitioning analysis classification I or II,No metastases (either pre-irradiated or not) and no resection cavity within the hippocampus or in a distance of 7 mm to the hippocampus (= hippocampal avoidance region, HAR).

Exclusion criteria are:

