PTV_WB-A or -B_	D_98%_ ≥ 25Gy D_mean_ ≤ 35 Gy	24Gy ≤ D_98%_ < 25Gy 35Gy < D_mean_ ≤ 37 Gy	D_98%_ < 24Gy D_mean_ > 37 Gy
PTV_met 51Gy (brain metastases)_	D_98%_ ≥ 48.4Gy D_2%_ ≤ 63.7Gy	47.4Gy ≤ D_98%_ < 48.4Gy 63.7Gy < D_2%_ ≤ 66.3Gy	D_98%_ < 47.4Gy D_2%_ > 66.3Gy
PTV_met 42Gy_ (brain stem metastases) PTV_res 42Gy_	D_98%_ ≥ 39.9Gy D_2%_ ≤ 52.5 Gy	39.06 Gy ≤ D_98%_ < 39.9Gy 52.5 Gy < D_2%_ ≤ 54.6 Gy	D_98%_ < 39.06 D_2%_ > 54.6 Gy

**PTV*_*WB-A*_

**Table 4 Tab4:** Organs at risk (OAR)

Parameter	Per Protocol	Minor Deviation	Major Deviation
Hippocampus in Treatment Arm A (HA-WBRT+SIB)	D_98%_ ≤ 9Gy D_2%_ ≤ 17Gy	9 Gy < D_98%_ ≤ 10Gy 17Gy < D_2%_ ≤ 18Gy	D_98%_ > 10Gy D_2%_ > 18Gy
Hippocampus in Treatment Arm B (WBRT+SIB)	D_98%_ ≥ 25Gy	24Gy ≤ D_98%_ < 25Gy	D_98%_ < 24Gy
Optical nerves Chiasm	D_2%_ ≤ 33Gy	33Gy < D_2%_ ≤ 35Gy (36Gy^a^)	D_2%_ > 35Gy (36Gy^a^)
Optical nerve, one-sided	D_2%_ ≤ 35Gy	35Gy < D_2%_ ≤ 37Gy	D_2%_ > 37Gy
Retina, one-sided	D_2%_ ≤ 33Gy	33Gy < D_2%_ ≤ 35Gy (49Gy^a^)	D_2%_ > 35Gy (49Gy^a^)
Lenses	D_2%_ ≤ 7Gy	7Gy < D_2%_ ≤ 10Gy	D_2%_ > 10Gy
Inner ear (in case of bilateral involvement)	D_2%_ ≤ 33Gy	33Gy < D_2%_ ≤ 35Gy (36Gy^a^)	D_2%_ > 35Gy (36Gy^a^)
Eyes	D_2%_ ≤ 33Gy	33Gy < D_2%_ ≤ 35Gy	D_2%_ > 35Gy
Brain stem (if metastasis inside the brainstem: brain stem-PTV_met_)	D_2%_ ≤ 33Gy	33Gy < D_2%_ ≤ 35Gy (51Gy^a^)	D_2%_ > 35Gy (51Gy^a^)

^a^in case of brain metastasis in the vicinity of OAR

Investigators enter pseudonymized patient data into electronic case report forms with automatic validation programs checking for completeness, consistency and plausibility. Randomization is performed centrally at the Medical Center – University of Freiburg and stratified by center, in blocks of variable length, based on computer-generated lists. The block lengths are documented separately and are not to be disclosed to the centers. Patients and assessors of NCF and MRI are blinded to treatment assignment. The use of different access rights to the electronic case report forms for treating radiation oncologists and for assessors of NCF and MRI assist in maintaining blinding.

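### The primary memory model leaves out age, a baseline covariate that the protocol itself links to memory decline; adding it would bring a small gain at a cost of one degree of freedom

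*Protocol article*

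**What the plan says.** The section on statistical planning and analysis lists the terms of the primary linear regression: "The model will include treatment and study center as independent variables and will adjust for the baseline learning scale word count of the VLMT". The outcome is the change in a raw word count (0 to 75) from baseline to 3 months. It is analysed in per-protocol patients alive at 3 months, and values missing for reasons other than death are multiply imputed.

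Age appears elsewhere in the article, but not in this model:

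- The Background says: "Although other factors contribute to memory decline, such as age, tumor growth or medication".
- The inclusion criteria admit "Age 18–80 years, male or female". The upper limit is there because the cognitive tests are not validated in older people.
- Randomization is "stratified by center, in blocks of variable length" (Study treatment and procedures), so the design does not balance age.
- Table 1 has demographic data documented at T0, so age is available for every patient.

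For comparison, the depression scores at baseline and 3 months do get an adjusted analysis of the primary endpoint, as a sensitivity analysis (Assessment of depression).

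**The concern.** The article does not leave the primary model open. It names the terms, and a baseline variable that its own rationale connects with memory is not one of them. The enrolled age range is wide, the endpoint is not described as age-standardised, and stratification does nothing for age.

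Two things are at stake. The first is precision: any variance in the 3-month change that age explains beyond baseline VLMT and center stays in the residual. The second is balance. About 33 patients per arm are analysed, and they are selected after randomization by survival and protocol adherence. Randomization therefore does not guarantee age balance in that set as it would, on average, among all 132. If the arms differ in age, the currently stated model does not correct for the part of the age effect that baseline memory does not already carry.

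**Working it through.** **Inputs from the article:** decline of 15 words (control) versus 7 (experimental), so a difference of 8; SD 15; two-sample t-test at one-sided 10%; 80% power; 66 evaluable; 50% evaluable; 132 randomized; 20 sites listed.

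**Assumed, because the documents give no figure:** the partial R² of age, meaning the share of residual variance that age explains beyond the other covariates, is taken as 1% to 10%.

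**1. The plan's own figure.** The standard error is 15 × √(4/66) = 3.69 words, and the noncentrality is 8 / 3.69 = 2.17 on 64 df. The exact t-test power is 80.8%; with 64 patients it is 79.9%. So 66 is the smallest even total that reaches 80%, and 66 / 0.5 = 132. The plan's figures reproduce, and no covariate adjustment is needed for them.

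**2. Adding age.** Residual SD = 15 × √(1 − R²), with one df fewer. The last column is the shift in the estimate when mean age differs between arms by 1.96 standard errors, which is 1.96 × √(4/66) = 0.48 SD of age, and age is left out: shift = 15 × √R² × 0.48.

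| Partial R² of age | SE (words) | Fall in SE | Power at 66 | N for 80% power | Shift (words) |
|---|---|---|---|---|---|
| 0% | 3.69 | – | 80.8% | 66 | 0 |
| 1% | 3.67 | 0.5% | 81.1% | 64 | 0.7 |
| 2% | 3.66 | 1.0% | 81.4% | 64 | 1.0 |
| 5% | 3.60 | 2.5% | 82.3% | 62 | 1.6 |
| 10% | 3.50 | 5.1% | 83.8% | 58 | 2.3 |

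If the SD of age were 10 years (assumed), 0.48 SD is 4.8 years.

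**3. The same on the stated regression.** With treatment, baseline score and 19 center terms, the residual df are 66 − 1 − 1 − 1 − 19 = 44. If baseline VLMT explains 20% of the variance (assumed), the residual SD is 15 × √0.8 = 13.42 and power without age is 86.8%. With age at 1%, 2%, 5% and 10% it is 87.1%, 87.3%, 88.1% and 89.4%. This treats the arms as balanced within center. The gain is again about 0.3 to 3 points.

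**4. Scale of the shift.** Against the 8-word target, 0.7 to 2.3 words is 0.72/8 = 9% to 2.29/8 = 29%. It arises only in the upper tail of chance imbalance; the typical shift is smaller.

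**The case against.** The strongest reply is that the model already adjusts for the baseline score of the same test, usually the best single predictor, and for the stratification factor. Whatever part of age shows in baseline memory is absorbed. Entry is also restricted on VLMT performance through the dementia exclusion, so the spread in memory is narrower than an 18–80 range suggests. The Background sentence says that age contributes to memory decline. It does not say that age predicts the 3-month change after irradiation given the baseline score. All of this stands, and it is why the gain is expressed only for age's residual share, with low values included.

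It also stands that omitting a baseline covariate neither biases a randomized comparison nor inflates type I error, since chance imbalance is already part of the standard error. That argument is weaker for a per-protocol survivor set than for all randomized patients. However, nothing in the article shows that age affects survival or adherence differently between arms, and the plan assumes similar survival in both. Selection is a reason for caution, not a demonstrated bias.

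A reader might go further and infer that an age imbalance passes in full into the treatment difference. It does not; only the part beyond baseline VLMT and center can.

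A reader might also infer that the survival analyses wrongly ignore RPA class, since entry requires "Recursive partitioning analysis classification I or II" and the article says only that "the corresponding endpoints will be analyzed with the Cox model". The documents do not support that. No unadjusted Cox model is stated, and the same section says: "Descriptive and explorative statistical analyses will be performed with respect to the secondary efficacy endpoints". Covariates for such models are commonly left to the full protocol or SAP, neither of which is shown. No event count, hazard ratio or RPA split is given either, so no loss could be computed.

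**Conclusion.** The point holds as a minor improvement to a model that the article does specify. The plan contains no error here: the test is valid, the 66/132 sample size is right, and the 80% power does not depend on age. Leaving age out gives away about 0.3 to 3 points of power and about 0.5% to 5% of the standard error. It also leaves a possible shift of 0.7 to 2.3 words under a 1.96-SE age imbalance.

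All these sizes rest on the assumed partial R² of 1% to 10%. If age adds almost nothing beyond baseline VLMT, the gain is close to nil. The case for acting is that the covariate is measured before treatment and needs no new data. Pre-specifying it also avoids a disputed post hoc adjustment should the ages turn out unequal.

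**What to change.** Add age, as a continuous variable, to the pre-specified covariates of the primary linear regression and to the imputation model for missing 3-month scores. Report the currently stated model (treatment, center, baseline VLMT) as a sensitivity analysis, so that the effect of the change is visible.

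The cost is one line of analysis wording and one degree of freedom, in a model where center may already use up to 19. No extra data collection and no change in sample size are needed. The choice should be fixed before any unblinded outcome data are seen.

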Simultaneous participation in other interventional trials which could interfere with this trial,Participation in a clinical trial within the last thirty days before the start of this trial, previous participation (randomization) in this trial,Known or persistent abuse of medication, drugs or alcohol,Persons who are in a relationship of dependence/employment with the sponsor or the investigator,Pregnancy, nursing or patient not willing to prevent a pregnancy during treatment,Cerebral lymphomas, metastases of germ cell tumors, small cell lung cancer,Acute neurological symptoms demanding an immediate start of radiation therapy,Central nervous system diseases or syndromes accompanied by cognitive deficits or radiological changes of the brain, e.g., dementia (VLMT-Learning < 39; VLMT-Delayed Recall < 7), major depression, clinically manifest hypertensive encephalopathy, carcinomatous meningitis,Previous brain irradiation (radiosurgery/stereotactic fractionated radiotherapy (SFRT)) of > 1 brain metastasis > 3 cm or > 3 brain metastases > 1 cm each,Previous brain irradiation < 3 months before start of treatment,Previous surgical resection (± adjuvant SFRT) of > 1 brain metastasis (biopsy allowed),Previous surgical resection of 1 brain metastasis < 4 weeks before start of treatment,Uncontrolled pretreated brain metastasis/−es after radiosurgery/SFRT,Last application of chemotherapy/ immunotherapy/ targeted therapy < 1 week before randomization,Radiotherapy planning conforming to organ at risk (OAR) constraints not feasible (including previous cranial irradiation),Benzodiazepines, barbiturates, topiramate, hydantoine as antiepileptic medication,More than 1 brainstem metastasis ≥5 mm,Brainstem metastasis > 2 cm,Brain metastasis > 3.5 cm,Resection cavity eligible for dose escalation > 3.5 cm.

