### Neurocognitive function assessment

The primary endpoint is the hippocampal-dependent episodic memory after treatment. Differential worsening of the two treatment groups from pre- to post-treatment is to be evaluated. The specific hypothesis to be tested is that 3 months after treatment – compared to pre-treatment – episodic memory decline in the HA-WBRT+SIB group is less severe than in the group of patients who received WBRT+SIB.

The primary endpoint will be assessed with the German version of the Auditory Verbal Learning Test [29], the VLMT (*Verbaler Lern- und Merkfähigkeitstest*) [30]. The VLMT is a standardized test with proven sensitivity to hippocampal dysfunction [31] and association with memory-related hippocampal activation [32]. Feasibility and adequacy of using the VLMT in similar settings have been demonstrated. Comparing two groups of patients with temporal lobe resections either including or sparing the hippocampus, Wagner et al. found that the patients whose hippocampus had been resected showed a significantly stronger decline of verbal learning performance after surgery as assessed with the VLMT [33]. The VLMT has also been used before in studies investigating the effects of WBRT for brain metastases [6] and chemotherapy for central nervous system lymphoma [34].

Among the secondary endpoints, episodic verbal memory and changes in delayed recall are assessed with the VLMT at additional time points: 9 and 18 months after treatment, in order to investigate acute and long-term effects of WBRT and the benefits of HA. Beyond 18 months after the end of WBRT, all patients who are still alive receive NCF assessment with VLMT once per year.

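### The superiority hypothesis is tested in a per-protocol set whose treatment criteria differ by arm, so exclusions after randomisation can bias the primary comparison

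*Protocol article*

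**What the plan says.** The hypothesis in Neurocognitive function assessment is directional: "episodic memory decline in the HA-WBRT+SIB group is less severe than in the group of patients who received WBRT+SIB". The sample size section plans to "reject the null-hypothesis of equality of treatment arms with 80% power", using a one-sided 10% t-test. This is a superiority test.

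The same section fixes the population: "The primary analysis population is the per-protocol set, defined as the group of randomized patients who had no major violations of eligibility criteria". A second condition follows, that treatment was given per protocol in the randomised arm. Sensitivity analyses are announced by reference to the full study protocol, without naming their populations.

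Table 4 has a column headed Per Protocol. Its row "Hippocampus in Treatment Arm A (HA-WBRT+SIB") has two upper limits, D98% ≤ 9 Gy and D2% ≤ 17 Gy. A minor-deviation band runs to 10 and 18 Gy, and values above that are major. The arm B row has one lower limit, D98% ≥ 25 Gy, with a minor band down to 24 Gy.

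Two eligibility rules bear on this. No metastasis or cavity may lie within 7 mm of the hippocampus. The exclusion list in Study population also contains "Radiotherapy planning conforming to organ at risk (OAR) constraints not feasible (including previous cranial irradiation").

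**The concern.** In a superiority trial, randomisation protects the comparison only if patients are kept in it as randomised. A per-protocol set selects on what happened after allocation. The selection criterion here is not the same in both arms: arm A must achieve active sparing, while arm B must reach a minimum dose. That minimum is the same 25 Gy figure that Table 3 sets for D98% of the whole-brain target, which in arm B includes the hippocampi. Whole-brain coverage therefore works towards the arm B criterion (without guaranteeing it) and against the arm A criteria.

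If patients who are hard to plan also have a different memory course, removing them from one arm shifts that arm's mean. The primary p-value and effect estimate would then mix the effect of hippocampal avoidance with the effect of selection. Sensitivity analyses, whatever they contain, do not change which result is primary.

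**Working it through.** **Inputs from Statistical planning and analysis.** Control decline of 15 words ("Assuming a mean decline after WBRT+SIB of 15 words in VLMT"); HA arm decline of 7 words ("improves to a 7 words decline after HA-WBRT+SIB"), so a difference of 8; SD 15; one-sided alpha 0.10; 80% power; 66 analysed; 50% of randomised patients available. Allocation is 1:1 (Trial design and setting).

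**1. Reproducing the plan.** SE = SD × √(1/nA + 1/nB), and noncentrality = 8/SE. The exact t-test gives power 0.799 at 32 per arm and 0.808 at 33 per arm, so 33 + 33 = 66. Then 66/0.50 = 132. Both stated figures reproduce.

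**2. What the 50% covers.** About 55% are expected to survive to 3 months. That leaves 55 − 50 = 5 percentage points, which the text attributes to patients unwilling or unable to do the test. No reserve for per-protocol exclusions is named.

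**3. Who leaves the set.** The population sentence does not cite Tables 2–4 and does not say whether minor or only major deviations remove a patient. That it refers to Table 4 is an inference, well supported by the column heading and by the reference to the randomised arm.

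**4. Order of planning and randomisation.** Table 1 puts both in the T0 column, and the article does not say which comes first. Infeasibility found after randomisation would itself breach an eligibility criterion, which is a second route out of the per-protocol set.

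**5. Illustration of bias.** *Assumptions, not from the article:* a fraction e of arm A alone is excluded, and those patients decline g words more than those kept. The kept mean then looks better by e × g. Starting from 33 per arm with no true effect, noncentrality = e × g/SE:

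| e | g (words) | e × g (words) | nA / nB | SE | One-sided type I error |
|---|---|---|---|---|---|
| 10% | 5 | 0.5 | 29.7 / 33 | 3.79 | 12.5% |
| 10% | 10 | 1.0 | 29.7 / 33 | 3.79 | 15.4% |
| 20% | 5 | 1.0 | 26.4 / 33 | 3.92 | 15.2% |
| 20% | 10 | 2.0 | 26.4 / 33 | 3.92 | 21.9% |

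Against the planned 8 words, 0.5/8 ≈ 6% and 2.0/8 = 25%.

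**6. Power at a true difference of 8 words.**

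| Excluded | nA / nB | Power |
|---|---|---|
| none | 33 / 33 | 80.8% |
| 10% of arm A only | 29.7 / 33 | 79.2% |
| 20% of arm A only | 26.4 / 33 | 77.2% |
| 10% of both arms | 29.7 / 29.7 | 77.6% |
| 20% of both arms | 26.4 / 26.4 | 73.9% |

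Steps 5 and 6 use an unadjusted t-test with SD 15. The planned regression adjusts for baseline score and centre, which would change these figures somewhat.

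**The case against.** The case for leaving the plan alone has real substance.

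- **Mitigation.** The 7 mm rule and the feasibility criterion remove many difficult patients before randomisation. A planning study preceded the trial, and every centre is asked to do a planning dummy run. Table 4 also has a minor-deviation band. This lowers the likely number of exclusions. It does not bring it to zero, for the reason in step 4.
- **Unseen document.** The full protocol may define the deviations and include an all-randomised analysis. That is possible, and the absence of those details from the article is no fault. The point rests on what the article states: which set is primary.
- **Phase II.** A one-sided 10% test can tolerate more error than a confirmatory trial. But the trial is randomised and formally tested, and its Discussion says the results could change treatment strategy.
- **Survivor rule.** Restricting to 3-month survivors is already a post-randomisation selection. This is correct, and the change proposed here does not remove it.

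A reader might infer three stronger things that the documents do not support:

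- *That exclusions will differ and will favour HA.* No rates are given, and the direction is unknown.
- *That patients who stop radiotherapy early are lost mainly from one arm.* Table 2 makes a departure from 12 treatment days a major deviation, but the schedule is the same in both arms. Some of these patients would also die before 3 months.
- *That unblinded radiation oncologists could steer the set.* The dose criteria are numerical plan values fixed well before the 3-month test, and the memory assessors are blinded.

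**Conclusion.** The point stands as a fault in the choice of primary population. A directional superiority test is run on a set formed after randomisation, and the Per Protocol criteria for the hippocampus differ between arms. Exclusions can therefore differ by arm and can bias the main result.

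The size cannot be known from the article. Under the stated assumptions the distortion runs from 0.5 words, which is minor, to 2.0 words, which roughly doubles the nominal 10% error. The loss of power is modest: 1.6 to 3.6 percentage points if only arm A loses 10–20%, and 3.2 to 6.9 if both arms do. The concern is mainly one of bias, not of power.

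**What to change.** Make the primary population all randomised patients, analysed in the arm assigned. Keep the stated 3-month survivor rule, baseline adjustment and multiple imputation. Keep the per-protocol set as a sensitivity analysis. List the deviations that exclude a patient, say whether minor ones count, and have them judged blind to VLMT results.

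The cost is an amendment or analysis-plan wording. The 66 and 132 are unchanged. No new data are needed, because Study treatment and procedures already continues the same assessments in patients who stop radiotherapy early. The downside is that non-adherent patients may dilute the estimated effect slightly.
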